## **7. SELECTION AND WITHDRAWAL OF PATIENTS**

### **7.1. Patient Inclusion Criteria**

Each patient must meet the following criteria for inclusion in the study:

1. Ability and acceptance to provide written informed consent;
2. Men or women between 18 – 64 years, inclusive;
3. Body Mass Index (BMI) of  $>18$  and  $<33\text{kg/m}^2$  ( $\text{BMI} = \text{weight (kg)} / [\text{height (m)}]^2$ );
4. Women of child-bearing potential (defined as less than 1 year post-menopausal or not surgically sterile) must be using an acceptable method of birth control (e.g., oral contraceptives, steroids, patch, intrauterine device [IUD], diaphragm or condom with spermicidal jelly or foam or abstinence, surgical sterility, or cervical cap) for a period of 35 days before the first dosing and must have a negative pregnancy test at the screening and Night 1 visits;

*Note:* Women using hormonal methods of birth control (e.g. oral contraceptives, patch, and steroids) must use an additional method of birth control during the study and for one month after the last dose.

5. Meets diagnostic criteria for primary insomnia as defined in DSM-IV;
6. Subjective sleep latency of  $\geq 45$  minutes at least 3 nights/week **and** subjective total sleep time  $\leq 6.5$  hours of sleep at least 3 nights/week based on sleep history (30 days prior to the screening visit);
7. Subjective sleep latency of  $\geq 45$  minutes at least 3 nights/week **and** subjective total sleep time  $\leq 6.5$  hours of sleep at least 3 nights/week based on sleep diary;
  - a. Note: The data from the seven consecutive days immediately preceding Visit 2 must be used for this criterion. The patient must have completed the sleep diary for at least 4 days out of the seven.
8. A mean LPS of  $\geq 30$  minutes on two consecutive placebo lead-in PSG with no night having a LPS less than 20 minutes;
9. Habitual bedtime between 9:00 PM and 1:00 AM at screening for at least one month prior to screening;
10. No history or evidence of restless leg syndrome or periodic limb movement disorder based on a Periodic Limb Movement with Arousal Index (PLMAI) score  $>10$  on diagnostic PSG;
11. No history or evidence of sleep apnea based on Apnea-Hypopnea Index (AHI) score  $>10$  on diagnostic PSG;
12. Willing and able to comply with study requirements and restrictions.

## **7.2. Patient Exclusion Criteria**

Patients will be excluded from the study if any of the following criteria apply:

1. History of drug or alcohol abuse as defined in DSM-IV, Diagnostic Criteria for Drug and Alcohol Abuse, within the 12 months prior to screening and/or regular consumption of alcoholic drinks (> 2 drinks/day or > 14 drinks/week);
2. A positive test for drugs of abuse at the screening visit or the first night of the single-blind period;
  - a. Note: A positive drug screen at Visit 1 due to medication use needs to be discussed with the medical monitor on a case-by-case basis.
3. Evidence of recent alcohol consumption as determined by breathalyzer test;
4. Smoke more than 10 cigarettes/day and not willing to follow the smoking restrictions in this study or use tobacco products during nightly awakenings;
5. History of psychiatric disorders including Major Depressive Disorder, Generalized Anxiety Disorder and delirium, within the 12 months prior to screening;
6. History of chronic obstructive pulmonary disease (COPD), seizures, sleep apnea, narcolepsy, circadian-rhythm sleep disorder, parasomnia or any other sleep disorder other than chronic insomnia;
7. Traveled more than three time zones 2 weeks prior to the screening visit or plan to travel across more than two time zones during the study;
8. Worked night, rotating, or split (period of work, followed by break, and then return to work) shift work within 1 month of the screening visit or plan to work these shifts during the study;
9. History or current evidence of hypercholesterolemia or hypertension, unless currently controlled and stable with protocol allowed medication 30 days prior to the first day of single-blind study medication;
10. History or current evidence of cardiovascular, hepatic, hematopoietic, renal, gastrointestinal or metabolic dysfunction.
11. History of intolerance and/or hypersensitivity to melatonin or melatonin agonists, or anyone who has taken melatonin or any other prescription or OTC medication that affect the sleep-wake cycle within 5 days of the single-blind medication;
12. Pregnant or lactating females;
13. Indication of impaired liver function (i.e., values  $\geq 2$  times the upper limit of normal for at least two of the following- aspartate aminotransferase, alanine aminotransferase, and total bilirubin);
14. Two consecutive abnormal vital sign measurements during the first screening visit. The following vital sign measurements will be considered abnormal for this study:
  - a. sitting systolic blood pressure of less than 90 mmHg or greater than 160 mmHG;

- b. a sitting diastolic blood pressure of less than 60 mmHg or greater than 100 mmHg;
  - c. a heart rate less than 40 or greater than 95 bpm.
15. Exposure to any investigational drug within 30 days of screening, including placebo;
  16. Participation in a previous BMS-214778/VEC-162 trial;
  17. Use of any prescription, OTC medication or sleep aids including herbal or other nontraditional sleep-inducing preparation within 7 days (or 5 half-lives of the drug, whichever is longer) of the single-blind medication except for the acceptable medications detail in [Section 8.2](#).
  18. Any other sound medical reason as determined by the clinical investigator.

### **7.3. Patient Withdrawal Criteria**

The term “discontinuation” refers to the patient’s premature withdrawal from the study before completing all scheduled evaluations.

Patients may be discontinued from the study for any of the following reasons:

- If in the Investigator’s judgment, continuation in the study may prove harmful to the patient. Such a decision may be precipitated by adverse events, including the occurrence of rash, changes in vital signs, physical examination, ECG, or laboratory tests. The Investigator will maintain autonomy in making medical/safety decisions regarding the patient’s continued participation in the trial. Clinically notable abnormalities in vital signs or laboratory tests are provided in [Appendices 21.2](#) and [21.1](#), respectively, to guide clinical focus regarding a patient’s continued participation.
- Noncompliance
- At the request of the patient.

Any time a patient discontinues from the study, the interactive voice response system (IVRS) should be notified.

Documented reason: It will be documented whether or not each patient completed the clinical study. If, for any patient, study treatment or observations were discontinued, the reason will be recorded (only 1 choice is acceptable) on the electronic case report form (electronic CRF). Acceptable reasons for a patient discontinuing participation in this clinical study are as follows:

1. protocol deviation (including noncompliance)
2. adverse event(s)(including abnormal laboratory values, abnormal test procedures, and pregnancy)
3. lost to follow-up
4. death
5. patient withdrew consent

6. unsatisfactory therapeutic effect
7. other (specify)

Patients who prematurely discontinue from the study (Early Termination) will undergo a complete safety assessment as detailed in the Schedule of Evaluation (see [Table 2](#)). Patients who discontinue because of an AE, abnormal laboratory value, or abnormal test result will be followed until resolution or for 30 days, whichever is less. If a patient elects to withdraw from the study, he/she will be informed that it is extremely important that the reason for discontinuation be reported and that all EOS assessments required by the protocol are performed.

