| Urinalysis                                                                                       |                                                                                                                                                                                                    |
| Gross and chemical exam                                                                          | color, appearance, specific gravity, pH, protein, glucose, ketone, blood, nitrite                                                                                                                  |
| Reflexive microscopic exam
(will be done if any of the
urinalysis testing is not negative) | RBC, WBC, epithelial cells, bacteria, casts, crystals                                                                                                                                              |

The clinical laboratory tests (hematology, chemistry, and urinalysis) will be performed by a certified central laboratory that will forward laboratory data to both the site and Vanda or its designee. Details regarding the collection, shipment of samples, reporting of results, and alerting of extreme values will be outlined in the Laboratory Manual, which will be supplied to all sites.

Values considered to be potentially clinically notable are provided in [Appendix 21.1](#) for the Investigator's guidance. Any laboratory test result that the Investigator considers clinically significant will be repeated once to rule out laboratory error. For tests where a

persistent abnormality is considered to be drug related, repeat analyses will be performed until the cause is determined and either a return to normality occurs or the Investigator deems the abnormality to be of no clinical significance. Any laboratory test result that the investigator considers clinically significant must also be recorded as an adverse event.

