#### **12.2.3. Adverse Event Follow-up**

Patients with non-serious adverse events that are ongoing at the patient's last study visit must be followed until resolution or for 30 days after the patient's last study visit, whichever comes first. Non-serious adverse events that are reported during the 7 days following the patient's last study visit will be recorded on the Adverse Events electronic CRF and followed until resolution or for up to the 30 days after the patient's last study visit, whichever comes first. Serious adverse events will be followed until the event resolves or the event or sequelae stabilize. Serious adverse events that are reported within 30 days of the patient's last study visit should be reported as indicated in [Section 12.5](#).

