#### **12.2.4. Adverse Event Reporting Period**

Adverse events are to be recorded in the source documents from the time of the patient's informed consent signature until the end of the patient's study participation. Each adverse event, both serious and non-serious, will also be reported on the Adverse Events electronic CRF. CRF Completion Instructions will be provided to each investigational site. If the patient reports or the Investigator learns of a new AE(s) up to 7 days after the patient's last study visit or a new SAE(s) up to 30 days after the patient's last study visit, the investigational site personnel will ensure that these data are recorded on the Adverse Events electronic CRF for the study. The period during which an SAE must be reported may be extended if there is a strong suspicion that the event being reported is related to the study medication or a study procedure.

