### 12.4.2. Post-study Adverse Event

At the last scheduled visit, the Investigator should instruct each patient to report any subsequent event(s) that the patient or the patient’s personal physician believes might reasonably be related to participation in this study. The Investigator should notify the study sponsor of any death or adverse event occurring at any time after a patient has discontinued or terminated study participation that may reasonably be related to this study. The Investigator should also notify the sponsor if they become aware of the development of cancer or a congenital anomaly in any offspring conceived subsequent to a patient’s study participation.

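### Section 7.3 caps follow-up at 30 days for patients who discontinue because of an AE without excepting SAEs, and so conflicts with section 12.2.3 for an SAE neither resolved nor stable at day 30

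*Protocol*

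**What the plan says.** The last paragraph of section 7.3 (Patient Withdrawal Criteria) covers patients who leave early because of an AE, an abnormal laboratory value or an abnormal test result. They "will be followed until resolution or for 30 days, whichever is less". The sentence does not separate serious from non-serious events, gives no starting point for the 30 days, and does not refer to section 12.2.3.

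Section 12.2.3 (Adverse Event Follow-up) does separate them. Two of its sentences set a 30-day limit, both for non-serious events and both counted from the last study visit. Events ongoing at the patient's "last study visit must be followed until resolution or for 30 days after" that visit, and events reported in the following 7 days "will be recorded on the Adverse Events electronic CRF and followed until resolution or for up to the 30 days after" it. The rule for serious events has no time limit: "Serious adverse events will be followed until the event resolves or the event or sequelae stabilize".

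Section 12.2.2 classes every AE as either serious or non-serious, so the AE in the section 7.3 sentence includes an SAE.

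**The concern.** A site whose patient withdraws because of a serious event would naturally turn to section 7.3, the withdrawal section. There it finds a ceiling of 30 days, because the rule takes the lesser of two periods. Section 12.2.3 requires the same site to continue until the event resolves or stabilises. No text gives either section precedence, and section 19.1 requires the protocol to be conducted as written.

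At stake is the outcome of a serious event that was bad enough to end participation and was still evolving a month later. If the site stops at day 30, the resolution or stabilisation that section 12.2.3 asks for may never be recorded. Efficacy results and AE counts are not at stake, since neither depends on how long an open event is followed.

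**Working it through.** The protocol states no figure on this point. The check is a comparison of two rules, followed by a bound on how many patients it could concern.

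**1. The two rules applied to an SAE that causes discontinuation**

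| State of the SAE | Section 7.3 | Section 12.2.3 | Compatible? |
|---|---|---|---|
| Resolved before day 30 | Stop at resolution | Stop at resolution | Yes |
| Open but stable by day 30 | Stop at day 30 | May stop once stable | Yes; stopping at day 30 meets both |
| Neither resolved nor stable at day 30 | Stop at day 30 | Continue | No |

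Only the last row is in conflict. For non-serious events the two sections broadly agree. The difference there is that section 12.2.3 counts from the last study visit, while section 7.3 names no start.

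**2. How many patients could be concerned**

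Inputs:
- Section 4.3.1: 45 enrolled and 39 randomised in the Phase II study; no SAEs; one discontinuation for an AE, judged unrelated.
- Section 4.3.2: 412 randomised in the transient insomnia study; no SAEs and no discontinuation for an AE.
- Section 14.2: 324 patients planned.

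Randomised subjects: 39 + 412 = 451, with 0 SAEs. With zero events in n subjects, the exact upper limit of the two-sided 95% interval is 1 − 0.025^(1/n).

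- n = 451: 1 − 0.025^(1/451) = 0.0081, or 0.81%. Then 324 × 0.0081 ≈ 2.6 patients.
- Counting the 45 enrolled, n = 45 + 412 = 457: 0.80%, again about 2.6 patients.

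For comparison, discontinuation for any AE was 1 of 451, or 0.2%.

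The 2.6 bounds patients with any SAE. The conflict needs two further conditions: the SAE causes discontinuation, and it is neither resolved nor stable at day 30. The protocol gives neither share. As an assumption only, suppose every such SAE led to discontinuation and 20% to 50% were still open at day 30. That gives 2.6 × 0.20 ≈ 0.5 to 2.6 × 0.50 = 1.3 patients, before removing those that are open but stable.

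**3. Whether other text lifts the cap**

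- Section 12.2.4: "The period during which an SAE must be reported may be extended" when a relation to study drug or procedure is strongly suspected. This concerns reporting.
- Section 12.4.2: the investigator notifies the sponsor of possibly related events "occurring at any time after a patient has discontinued or terminated study participation". This is notification.
- Section 12.5.1: follow-up reports supply what the first report lacked, such as an end date, and significant new information on ongoing SAEs goes to the sponsor's designee promptly.

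All three govern what reaches the sponsor. None changes how long section 7.3 says the patient is followed.

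**The case against.** The strongest reply is that section 12.2.3 is the dedicated follow-up section. It separates serious from non-serious events and does not exempt discontinued patients, so the specific SAE rule should govern. Section 7.3 states a follow-up length and does not forbid a longer one, so a site that follows an SAE to stabilisation breaks no explicit prohibition. Section 12.5.1 adds that a site can hardly supply an end date without staying in contact.

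Much of this stands as to practical risk: many sites would continue. It does not remove the conflict. Section 7.3 is specific in its own way, to patients who stop because of an AE. A rule that takes the lesser period cannot be read as a minimum that section 12.2.3 extends. The reporting duties also work less well once a site has stopped following the patient.

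Three stronger readings are tempting, and the protocol does not support them.

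- **Every SAE still open at day 30 is in conflict.** Section 12.2.3 is also met by stabilisation, so an open but stable event satisfies both sections.
- **The cap also overrides laboratory follow-up.** For persistent abnormalities considered drug related, section 12.1.1 repeats the tests "until the cause is determined and either a return to normality occurs or the Investigator deems the abnormality to be of no clinical significance", and it says that clinically significant results "must also be recorded as an adverse event". That is a narrow rule that can be read as an addition to the general AE rule. The decreased hematocrit (n = 18) and hemoglobin (n = 10) counts in section 4.3.1 do not size the problem: prevalence was similar on placebo, and nothing is said about relatedness or persistence.
- **Pregnancy is capped at 30 days.** Section 7.3 lists pregnancy under the AE reason for discontinuation, but its follow-up sentence does not name it, and section 12.1.6 requires follow-up to outcome.

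**Conclusion.** The inconsistency is real and narrow. Read with the AE classification in section 12.2.2, section 7.3 sets a 30-day ceiling that section 12.2.3 does not allow for an SAE that causes discontinuation and is neither resolved nor stable at day 30. Section 7.3 also leaves the start of the 30 days undefined.

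Very few patients are affected: at most about 2.6 of 324 if the 0.81% upper limit from the prior studies applied, and only a fraction of those. That bound rests on short studies in healthy volunteers and may understate the SAE rate in patients treated for 5 weeks. The protocol offers no figure from which to derive a higher rate. Sample size, power, efficacy results and AE counts are untouched. The consequence is possible early closure of SAE follow-up, partly mitigated by section 12.5.1. It should be corrected because the rule as written is wrong and the correction costs almost nothing.

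**What to change.** Replace the follow-up sentence in section 7.3 with two, for example: *A patient who stops because of a non-serious AE, or an abnormal laboratory or test result, is followed until it resolves, up to a maximum of 30 days from the last study visit. An SAE is followed as section 12.2.3 requires.*

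Section 12.2.3 needs no change. At most, section 7.3 could add a pointer to section 12.1.1 for persistent laboratory abnormalities considered drug related.

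The cost is one sentence rewritten as two. No visit, procedure or analysis is added, because section 12.2.3 already requires the longer follow-up of SAEs.

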## **8. TREATMENT OF PATIENTS**

### **8.1. Dosing**

This section describes the dosing schedule for the Lead-in, the Evaluation, and the Wash-out Periods.

#### **During the Lead-in Period:**

- A single oral dose of placebo will be administered to the patients on Visit 2 thirty minutes ( $\pm$  5 minutes) prior to lights off under single-blind conditions. The placebo capsule will be taken with water. Patients will continue to ingest one placebo capsule (single-blind) every night approximately 30 minutes prior to their planned bedtime until Night 1. Patient will take the medication with water.

#### **During the Double-Blind Evaluation Period:**

- On Visits 3-6, study medication will be dispensed by study personnel under double-blind conditions. Patients will take oral doses of 20 mg VEC-162, 50 mg VEC-162 or placebo (blinded) 30 minutes ( $\pm$  5 minutes) prior to lights off. Capsules will be taken with water.
- While at home, patients will continue to take oral doses of either 20 mg VEC-162, 50 mg VEC-162 or placebo approximately 30 minutes before planned bedtime. Capsules will be taken with water. Patients and study personnel will remain blinded as to the contents of the bottles.

#### **During the Wash-out Period:**

- A single oral dose of placebo will be administered to the patients on Visit 7 (Night 36  $\pm$  2 days) 30 minutes ( $\pm$  5 minutes) prior to lights off under single-blind conditions. The placebo capsule will be taken with water.

### **8.2. Concomitant Medications**

All concomitant illnesses will be treated in accordance with prevailing medical practice. The study staff will record the names of all drugs prescribed, duration of usage, and indication on the Concomitant Medication electronic CRF.

The following drugs (drug classes) are permitted during the study:

- Ibuprofen or acetaminophen
- Birth control medication
- Colace (Docusate Sodium)
- Fiber laxatives

- Vitamins and supplements (except ones with CNS or sedative effects or those that can alter the sleep-wake cycle)
- Baby aspirin
- Lactaid®
- The following statins: fluvastatin (Lescol®), pravastatin (Pravachol®), and rosuvastatin (Crestor®)
- Anti-Hypertensive medication except for the following drugs or drug classes:
  - Calcium channel blockers such as amlodipine, felodipine, isradipine, mibefradil, nicardipine, nifedipine, nimodipine, nisoldipine, diltiazem, verapamil
  - Others: Eplerenone, Ambristentan, alliskiren, Amlodipine Besylate/Benazepril, Hydrochloride, Amlodipine Besylate/Valsartan, Bisoprolol fumarate/hydrochlorothiazide, bosentan, Candesartan Cilexetil/Hydrochlorothiazide, diazoxide
- Topical steroids
- Saline nasal spray
- Saline eye drops
- Additional medications may be permitted on a case-by-case basis if pre-approved by the medical monitor

### **8.3. Treatment Compliance**

Compliance at the clinical site during inpatient visits will be assured by administration of the study drug under the supervision of a member of the study team. Compliance in this study will be assessed by the Investigator. The Investigator will consider capsule use (returned capsules) and feedback from study staff when assessing compliance. An overall assessment of compliance will be documented in the CRFs. Patients with a compliance of less than 80% will be re-educated by the Investigator or study staff on the importance of taking the study medication properly.

Any overdose that occurs during study participation must be reported to Covance Drug Safety Services (Vanda's designee) using the Study Drug Overdose Report Form.

